# **7 Research interventions**

## **7.1 Intervention content**

### **7.1.1 Study intervention description**

In accordance with routine clinical practice, the fracture was reduced by closed manipulation under local anesthesia. Imaging X-ray films were used to determine whether a satisfactory closed reduction was achieved after reduction. Splint and cast were used for external immobilization according to the group. Active finger activity was encouraged after immobilization. External immobilization was removed for an average of 6 weeks, and wrist rehabilitation activities commenced.

[figure not shown]

### **7.1.2 Dosing and Administration**

Not applicable

### **7.1.3 The items and number of clinical and laboratory tests to be performed**

The fractured wrist was X-rayed examinations four times after reduction, 2weeks, 6 weeks, and 12weeks, to assess displacement and healing

## **7.2 Preparation/Handling/Storage/Accountability**

### **7.2.1 Accountability**

The researcher should record the brand and type information of the splint and cast.

### **7.2.2 Formulation, appearance, packaging and labeling**

Not applicable

### **7.2.3 Product storage and stability**

Storage under normal conditions, no special requirements

### **7.2.4 Preparation**

All surgeons involved in this study were trained in the treatment of distal radius fractures and the application of splints and casts. In accordance with routine clinical practice, the fracture was reduced by closed manipulation under local anesthesia. Splint and cast were used for external immobilization according to the group.

## **7.3 Measures to minimize bias**

Randomization, Allocation Concealment, and Blinding

## **7.4 Follow-up and Adherence**

The observation period was 3 months, and participants were evaluated clinically at 3 days, 7 days, 2 weeks, 6 weeks, and 12 weeks after initiation of treatment, with X-ray evaluation at 2 weeks, 6 weeks, and 12 weeks.

The researchers should carefully implement informed consent so that the subjects fully understand the test requirements and cooperate with the researchers. The surgeon treated the participants free of charge and directed rehabilitation training

### 7.5 Research Intervention Commitment

Participants were immobilized in topology-optimized splints and casts and recovered at the end of the study, while various situations that arose during the intervention were recorded and solutions were discussed in time

### 7.6 Research Flow Chart

|                                                 | Screening Period | Treating Period |      |       |       | Follow-up Period |
|-------------------------------------------------|------------------|-----------------|------|-------|-------|------------------|
| Time                                            | Day0             | Day3            | Day7 | Week2 | Week6 | Week12           |
| Basic information                        |                  |                 |      |       |       |                  |
| Informed Consent Form                           | √                |                 |      |       |       |                  |
| Medical history, past medical history           | √                |                 |      |       |       |                  |
| Inclusion/exclusion criteria                    | √                |                 |      |       |       |                  |
| Subjects were randomized                        | √                |                 |      |       |       |                  |
| General evaluation and safety evaluation |                  |                 |      |       |       |                  |
| visual analogue scale (VAS) scores              | √                | √               | √    | √     | √     | √                |
| Grading of swelling degree                      | √                | √               | √    | √     | √     | √                |
| radiographic parameters                         | √                |                 |      | √     | √     | √                |
| Gartland-Werley (G-W) wrist scores              |                  |                 |      |       | √     | √                |
| Adverse Event Reporting                         |                  | √               | √    | √     | √     | √                |
| Summary of research completion                  |                  |                 |      |       |       | √                |
| Drug combination                                |                  | √               | √    | √     | √     | √                |
| Other work                               |                  |                 |      |       |       |                  |
| Assign random numbers                           | √                |                 |      |       |       |                  |
| Distribution research instrument                | √                |                 |      |       |       |                  |
| CRF filling                                     | √                | √               | √    | √     | √     | √                |

## 8 Study intervention termination and subject termination/withdrawal

### 8.1 Study intervention termination

During the course of the study, if significant fracture displacement or serious complications such as compartment syndrome occur, the intervention study should be stopped and immediate surgical treatment should be performed, and the available data should be recorded in detail.

After the study intervention was discontinued, the subjects continued to follow up regularly to observe the swelling, pain and movement of the affected limb, and to take reasonable measures.

The termination of the study intervention does not mean that the entire study is termination, and the remaining study procedures continue in accordance with the current treatment protocol for distal radius fractures.

### 8.2 Subject termination/withdrawal

The researcher can suspend or withdraw the research object when the research object has the following conditions:

- (1) Pregnancy
- (2) Significant research intervention noncompliance
- (3) In the event of significant fracture displacement or other clinical conditions, it is no longer in the subjects' best interest to continue participating in the study

(4) The disease progresses to the point where discontinuation of the study intervention is required. Subjects' reasons for termination/withdrawal from the study should be recorded on the case report form, and subjects who signed informed consent and were randomly assigned but did not receive the study intervention will be replaced. Study subjects who sign informed consent, are randomly assigned, receive the study intervention and then withdraw will be or not replaced.

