### **8.3 Lost to follow-up**

Subjects who stop scheduled study follow-up, fail to complete prescribed study procedures, or cannot be contacted by the investigator may be considered lost to follow-up. Notify subjects in time window in advance to reduce lost follow-up and missing data.

Each subject should leave a detailed contact address, telephone number, ID card and other information, and the doctor should leave his or her contact number with the subject, so that the subject can seek the doctor's help when the condition changes, which is also conducive to the doctor to keep abreast of the condition changes, remind the subject to return visit in time, and avoid the loss of visit.

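### Section 8.2 lets a researcher who knows the arm withdraw a patient from the study for undefined noncompliance, without saying that follow-up continues, so the week-12 G-W rating may be lost selectively

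*Protocol*

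**What the plan says.** Section 8.2 gives the authority: "The researcher can suspend or withdraw the research object when the research object has the following conditions". Its second ground is "2) Significant research intervention noncompliance". The protocol does not say what makes noncompliance significant, whether hours worn, removals or missed visits.

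Once a patient is withdrawn, 8.2 requires that the "reasons for termination/withdrawal from the study should be recorded on the case report form". It then turns to replacement, and leaves open whether patients who were treated and then withdrew are replaced. It says nothing about further visits.

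Section 8.1 deals with stopping the intervention. Its first paragraph concerns significant displacement and serious complications. The next two are worded generally: "After the study intervention was discontinued, the subjects continued to follow up regularly", and "The termination of the study intervention does not mean that the entire study is termination, and the remaining study procedures continue".

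Other relevant places:

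- Section 5.1 describes the trial as analyst-blind, and under 6.4 the envelope is opened in front of the patient.
- The flow chart in 7.6 schedules "Gartland-Werley (G-W) wrist scores" only at weeks 6 and 12.
- Section 7.1.1 states: "External immobilization was removed for an average of 6 weeks, and wrist rehabilitation activities commenced".
- Section 8.3 aims to limit missing data: "Notify subjects in time window in advance to reduce lost follow-up and missing data".

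**The concern.** Whether a noncompliant patient is rated at week 12 is a matter of trial conduct. An analysis plan can impute or bound a missing rating, but it cannot collect one. Under 8.2 the decision to remove the patient rests with someone who knows the arm and applies an undefined standard. Tolerance of a light, ventilated splint and of a cast may well differ, so withdrawals on this ground may differ by arm too. If withdrawal ends assessment, the primary outcome goes missing in a way related to treatment and possibly to prognosis.

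Timing makes this harder to repair. Device noncompliance arises mostly while the device is worn, up to about week 6, and the first G-W rating is due at week 6. If a site treats withdrawal as the end of assessment, a patient withdrawn before then has no G-W rating from which a later one could be estimated.

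**Working it through.** **1. What the text settles**

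| Question | Section 8.1 | Section 8.2 |
|---|---|---|
| What ends? | The intervention | Participation in the study, judging by the heading and the case report form sentence |
| Noncompliance named? | No | Yes, ground (2) |
| Significant displacement | Intervention stops, follow-up continues | Ground (3) for withdrawal |
| Need to discontinue the intervention | Does not end the study | Ground (4) for withdrawal |
| Follow-up afterwards | Continues | Not mentioned |
| Replacement | Not mentioned | Left open for treated patients |

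The two sections treat the same events differently, and neither refers to the other. So it cannot be assumed that 8.1 carries over to ground (2). Two sites could act differently and each be following the protocol.

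**2. The plan's own figure**

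Inputs from 5.3: effective rates of 96% and 77% at 3 months, two-sided 5% error, 80% power, 10% drop-out. With the pooled-variance formula and a mean rate of 0.865:

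n = [1.96 × √(2 × 0.865 × 0.135) + 0.8416 × √(0.96 × 0.04 + 0.77 × 0.23)]² / 0.19² = 49.6, so 50 per arm and 100 in total. Then 100 × 1.10 = 110, which matches the protocol. The sample size is not in dispute. With 1:1 allocation there are 55 per arm.

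**3. Range left open, with no assumption about noncompliers**

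Each unrated patient in an arm of 55 could be effective or not, so the arm's rate is undetermined by 1/55:

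- 1 unrated: 1/55 = 1.8 points
- 3 unrated: 3/55 = 5.5 points
- 5 unrated: 5/55 = 9.1 points

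The planned difference is 19 points. These are widths of uncertainty, not biases, and they hold for an outcome missing for any reason.

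**4. Illustration with assumed inputs**

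Let d be the compliers' effective rate minus the noncompliers', taken as equal in both arms, and f the fraction of an arm withdrawn and unrated. The rate among rated patients exceeds the rate in all randomised patients by f × d, so the bias in the difference is d × (f_splint − f_cast).

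| Gap in f between arms | d = 0 | d = 10 | d = 20 | d = 30 |
|---|---|---|---|---|
| 0% | 0 | 0 | 0 | 0 |
| 5% | 0 | 0.5 | 1.0 | 1.5 |
| 10% | 0 | 1.0 | 2.0 | 3.0 |

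Entries are in points. The sign depends on which arm loses more.

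The 3.0-point entry is strained. In the splint arm, f = 10% and d = 30 with 96% overall means compliers at 99% and noncompliers at 69%. Then 0.10 × 31 = 3.1 of the 4.0 failure points (77.5%) fall in one tenth of patients. At d = 10 the rates are 97% and 87%, and the share is 1.3/4.0 = 32.5%.

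**5. Drop-out allowance**

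10% of one arm is 5.5 patients, which is 5% of 110 and half of the 11-patient allowance. Losses of this size fit within the planned drop-out. That allowance protects power; it does not protect against loss that differs by arm.

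**The case against.** The best case for the protocol is that it already leans towards follow-up. The general paragraphs of 8.1 name no cause and can cover a noncomplier. The split between 8.1 and 8.2 is not clean, and 8.2 offers suspension as well as withdrawal. Section 5.2 defines completion by outcome assessment and follow-up, with no condition about wearing the device. Section 8.3 tells sites to limit missing data. All of this stands, and it makes continued follow-up a plausible reading. It does not settle the matter, because grounds (3) and (4) allow patients to leave the study where 8.1 would keep them, and because 8.2 contemplates replacing treated patients who withdraw.

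A reader might infer three stronger points that the document does not support:

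- *That 8.2 forbids the week-12 visit, or that every early noncomplier has no G-W rating.* Section 8.2 is permissive. The absence of any rating follows only on the restrictive reading, and it would equally affect anyone lost before week 6 for another reason.
- *That 8.2 breaches an intention-to-treat commitment.* The sentence in 10.1 names intention-to-treat and per-protocol together and cannot be read as a clear commitment to either.
- *That the rule favours the splint or inflates the type I error by a known amount.* Suppose the true rate is 77% in both arms and three splint-arm failures alone go unrated. The apparent splint rate is then 0.77 × 55 / 52 = 81.4%, a spurious 4.4 points. That assumes wholly selective loss in one direction, for which the protocol gives no ground.

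**Conclusion.** The concern holds as a badly fixed conduct rule. Section 8.2(2) gives an unblinded researcher discretion, under an undefined standard, to withdraw a randomised patient from the study, and it does not state that outcome assessment continues. The consequence is a risk that the week-12 G-W rating is missing selectively by arm. Week 12 is taken as the primary time point from the 3-month rates in 5.3.

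Size and direction cannot be derived. The assumption-free statement is 1.8 points of one arm's rate left open per unrated patient. The illustrated bias runs from 0 to 3.0 points in either direction, rests wholly on assumed inputs, and is strained at its upper end. The change is worth making because it removes an avoidable source of missing primary outcome at almost no cost, not because a bias has been shown.

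**What to change.** Amend 8.2 as follows.

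- **Ground (2):** make noncompliance a reason to stop or change the device only, not to leave the study. State that the patient remains in follow-up, has the scheduled week-6 and week-12 G-W ratings unless consent is withdrawn, and is analysed in the randomised arm. The undefined threshold then no longer decides whether the outcome is collected.
- **Grounds (1), (3) and (4):** leave them as they are, except that the clinical G-W assessment is taken at week 12 where it is safe and the patient agrees, with no added X-ray obligation. Carrying all of 8.1 over to every ground would go too far: it could keep a pregnant patient on the scheduled study X-rays and override a withdrawal made in the patient's best interest.

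The cost is wording in one section. No visit or measurement is added to the schedule, and the sample size does not change. The downside is that retained noncompliers may slightly dilute the observed difference.

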#### 5.3 Sample size

The sample size was calculated by PASS software (NCSS, Kaysville, UT) with sample allocation ratio of 1:1 between 2 groups with reference to other studies ( $n=94$ ). The difference in G-W score effective rate between the intervention group (96%) and the control group (77%) was 19% at 3 months, with a 2-sided 5% of type I error probability, and an 80% of power, allowing drop-out rate of 10%, a total of 110 cases were finally required for enrollment.

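### Sections 8.1 and 8.2 conflict on whether a patient whose fracture displaces stays in the study, so some treatment failures can drop out of the week-12 effective rate

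*Protocol*

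**What the plan says.** Section 8.1 (Study intervention termination) says that "if significant fracture displacement or serious complications such as compartment syndrome occur, the intervention study should be stopped" and that surgery follows. It then says: "After the study intervention was discontinued, the subjects continued to follow up regularly". It adds that ending the intervention is not the end of the study and that the remaining study procedures go on.

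Section 8.2 (Subject termination/withdrawal) lists conditions under which the researcher may suspend or withdraw a subject. Item (3) begins "In the event of significant fracture displacement or other clinical conditions" and is tied to continued participation no longer being in the subject's best interest. Item (4) is disease progression to the point where the intervention has to be discontinued. Subjects who are randomised but never receive the intervention are to be replaced. Those who "receive the study intervention and then withdraw will be or not replaced" have no fixed rule.

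Section 5.3 sizes the trial on the G-W effective rate at 3 months, taken as 96% for the splint and 77% for the cast. The other inputs are a two-sided 5% error, 80% power and a 10% loss, and the section concludes: "allowing drop-out rate of 10%, a total of 110 cases were finally required for enrollment". Section 10.2 names the G-W score as the primary endpoint. The flow chart in section 7.6 schedules it at weeks 6 and 12 only. Section 2.4.3 says that significant displacement and serious complications can occur but are clinically rare.

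**The concern.** One event leads to two different study dispositions. Under 8.1 the patient stops the device and stays in the study. Under 8.2(3) or 8.2(4) the same patient may leave it. The two centres could handle identical patients in opposite ways and both comply with the protocol.

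This matters for the primary result because holding the reduction is what the splint and the cast are for. A patient withdrawn for early displacement has no week-12 G-W score, and the reason for the missing score is failure of the treatment under test. If withdrawals differ between arms, the rate among those still observed is raised more in the arm that loses more failures. The envelope is opened in front of the patient (section 6.4) and the trial is described as blind only at the analyst level (section 5.1), so whoever decides on withdrawal may know the arm.

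The open replacement rule adds to this. A withdrawn failure could be replaced by a new patient, which hides the loss in the final count.

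**Working it through.** **The passages side by side**

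| Event | Section 8.1 | Section 8.2 |
|---|---|---|
| Significant displacement | Intervention stops, follow-up continues | (3): may be withdrawn from the study, if best interest so requires |
| Intervention has to be discontinued | Not the end of the study | (4): a withdrawal ground in itself |
| Treated patient then withdraws | Not addressed | Replaced or not: undecided |

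Item (3) can be read as an exception to 8.1, because of its best-interest condition. Item (4) has no such condition and runs directly against 8.1.

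**The plan's own sample size**

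Inputs from section 5.3: 96% v 77%, two-sided 5%, 80% power, 10% drop-out, "sample allocation ratio of 1:1 between 2 groups". With the pooled-variance formula and no continuity correction, the mean rate is 0.865 and

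n per arm = [1.96 × √(2 × 0.865 × 0.135) + 0.8416 × √(0.96 × 0.04 + 0.77 × 0.23)]² / 0.19² = 49.6, rounded up to 50.

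That is 100 evaluable patients. Then 100 × 1.10 = 110, the stated figure; 100 / 0.90 gives 112 after rounding up to equal arms. The total is not in dispute. At these rates about 0.04 × 50 = 2 splint and 0.23 × 50 = 11.5 cast patients would fail, so a few withdrawals are a sizeable part of the failures, above all in the splint arm.

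**How withdrawal moves the rate**

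Let p be the true success rate among all randomised in an arm, and d the share that displaces. Assume that every displaced patient would fail and is withdrawn. The rate among those left is p / (1 − d).

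Assumptions, none from the protocol: p = 0.86 in both arms (close to the average of the design rates, 86.5%), 55 per arm, d as shown. The last column is the share of simulated trials (200,000 per row) in which a two-sided 5% chi-square test on the remaining patients declares the splint superior. The nominal value is 2.5%. Differences are taken from unrounded rates.

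| d, splint v cast | Observed rates | False difference | Splint falsely superior |
|---|---|---|---|
| equal (e.g. 2% v 2%) | 87.8% v 87.8% | 0.0 points | 2.5% |
| 3% v 2% | 88.7% v 87.8% | 0.9 points | 3.5% |
| 5% v 2% | 90.5% v 87.8% | 2.8 points | 6.5% |
| 8% v 2% | 93.5% v 87.8% | 5.7 points | 16% |
| 10% v 2% | 95.6% v 87.8% | 7.8 points | 29% |

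With the arms reversed (2% v 10%), the cast is falsely declared superior in about 29% of trials.

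**The opposite direction at the planning rates**

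If 10% of the cast arm fail through displacement and are withdrawn, and no splint patients are, the cast rate becomes 0.77 / 0.90 = 85.6%. The difference falls from 19.0 to 96 − 85.6 = 10.4 points, and power from about 80% to about 43% (49.5 evaluable per arm before withdrawal). Ten per cent is again an assumption, and a high one for an event called rare.

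**The case against.** Section 8.2 is permissive. The researcher may withdraw a patient, and item (3) applies only where staying in the study is no longer in the patient's interest. Section 8.1 can be taken as the default. A reader might infer that every displaced patient leaves the study, but the text does not say so. It supports only that some failures can be removed. This part of the objection stands.

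The protocol calls the event rare, so a reader should not take the 16% and 29% rows as the expected size. At small differences in displacement the inflation is slight, at equal rates there is none, and partial withdrawal shrinks it further. This also stands.

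A reader might also infer that withdrawing four of 50 splint patients would overturn the result at the design rates. The numbers do not allow it. If four are withdrawn as failures and the other 46 succeed at 96%, the rate among all 50 is 46 × 0.96 / 50 = 88.3%, which is not the design rate of 96%.

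Finally, the protocol does not define displacement as a G-W failure. A patient operated on under 8.1 could score well at week 12. How such patients count is a choice of estimand that may properly sit in a statistical analysis plan, so its absence from section 10 is not an error in itself. An analysis plan cannot, however, recover week-12 scores that were never collected, and it does not settle a conflict between two conduct rules.

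**Conclusion.** The conflict between 8.1 and 8.2(3)–(4) is real, and the replacement rule for treated patients is undecided. Followed as written, the protocol can lose week-12 G-W data because the treatment failed, and the resulting bias can favour either arm. Its size cannot be fixed from the document. Under the assumptions shown, the one-directional false-positive rate runs from the nominal 2.5% at equal displacement to 6.5% at 5% v 2% and 29% at 10% v 2%.

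The figures rest on all displaced patients failing and all being withdrawn. They also rest on the week-12 effective rate being the primary measure, which is inferred from sections 5.3 and 10.2 because section 9.1 shows no content.

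This should be fixed. The text does not show that failures are systematically removed, so it is not a flaw that by itself invalidates the primary comparison.

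**What to change.** - Reconcile 8.1 and 8.2 so that ending the study intervention does not by itself end study follow-up.
- State that the week-12 G-W score is collected for every randomised patient, whatever treatment followed, unless consent is withdrawn. Section 8.1 names swelling, pain and movement but not G-W, so it is worth naming.
- State that randomised patients who received the intervention and then withdraw are not replaced, and that they stay in the intention-to-treat analysis in their assigned arm. Section 10.1 names intention-to-treat and per-protocol together in one unclear sentence and does not settle this.
- Add one sensitivity analysis of the primary rate in which patients who had surgery for displacement or a serious complication before week 12 count as not effective. Tie it to surgery for those reasons, not to stopping the device, because immobilisation ends at about week 6 by design.

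The decision to stop the intervention or to operate is left as it is, and no clinical rule is proposed. The cost is a few sentences and one extra analysis. The sample size does not change, and no visits are added, because the week-12 visit is already scheduled and 8.1 already keeps these patients in follow-up.

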### 5 Study Design

#### 5.1 Overall design

The study was a multicenter, randomized, analyst-blind controlled trial. Each subject was randomly assigned to an intervention group or a control group in chronological order of visit. The intervention group was immobilization with topology-optimized splint, and the control group was immobilization with cast. After 6 weeks of immobilization, the patient was instructed to perform wrist rehabilitation exercises and the clinical outcomes were evaluated.

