## **6.4 Methodology of research subject assignment**

Patients were randomly assigned to the topologically optimized splint group or the cast group in 1:1 ratio. Random sequence list generated by SAS (Strategic Application Software, version 9.4; SAS Institute Inc) were sealed in opaque envelopes and distributed to each center. The envelope was opened in front of the patient in chronological order of the patient's visit.

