## **10 Statistical Analysis**

### **10.1 General Method**

During statistical analysis, the following steps will be taken: first, an examination of the number of completed cases and dropout status of the patients; then, an analysis of the baseline characteristics related to demographics for the two groups at the time of patient inclusion, assessing comparability between the study group and the control group; efficacy evaluation will involve determining efficacy indicators and comparing the efficacy between the two groups; safety evaluation will include a comparison of laboratory indicators and clinical adverse reactions.

All statistical tests will be two-tailed, and a p-value less than or equal to 0.05 will be considered statistically significant for the tested differences.

Data analysis was consistent with the principle intention-to-treat (ITT) of per-protocol (PP). For quantitative variables, descriptive statistics will include means, standard deviations, medians, minimum values, maximum values, lower quartiles (Q1), upper quartiles (Q3), and for categorical variables, the description will include counts and percentages for each category.

Comparisons between the two groups for general characteristics will be analyzed using appropriate methods based on the type of indicator. The comparison between the two groups used Student's t-test or the Mann-Whitney U-test for continuous variables, and chi-square test or Fisher's exact test for categorical variables. For repeatedly measured data, we used a linear mixture model for statistical analysis, with participants as random effects, time and group as fixed effects, multiple comparisons of data were correction by Bonferroni. Complications were analyzed by calculating the risk ratios and 95% confidence interval.

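### Randomised patients may be replaced once the arm is known, and no primary analysis population is fixed, so randomisation is not guaranteed to protect the week-12 Gartland-Werley comparison

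*Protocol*

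**What the plan says.** **Replacement.** Protocol Section 8.2 states that "subjects who signed informed consent and were randomly assigned but did not receive the study intervention will be replaced". For the next group, those who "are randomly assigned, receive the study intervention and then withdraw will be or not replaced", it gives no criterion and names no one to decide.

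**Knowledge of the arm.** Section 6.4: "The envelope was opened in front of the patient in chronological order of the patient's visit". Section 5.1: "The study was a multicenter, randomized, analyst-blind controlled trial". Patient and surgeon therefore know the arm before any refusal, withdrawal or replacement.

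**Grounds for leaving.** Section 8.2 lets the researcher withdraw a patient for "Significant research intervention noncompliance", and also where significant fracture displacement or another clinical condition makes staying in the study no longer in the patient's interest. Section 8.3 adds that patients who "fail to complete prescribed study procedures, or cannot be contacted by the investigator may be considered lost to follow-up". Section 8.1, by contrast, keeps patients in follow-up after the intervention has been stopped.

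**Analysis population.** Section 10.1 reads: "Data analysis was consistent with the principle intention-to-treat (ITT) of per-protocol (PP"). Section 10.2 names the tests for the G-W score but no population.

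**The concern.** A randomised comparison is protected only if everyone allocated is followed and counted in the allocated arm. Here the decision not to start, or to leave, is made by people who know the arm. The devices differ visibly, and Section 2.2 itself describes the cast as bulky and uncomfortable, so refusal or non-compliance that differs by arm is foreseeable. Non-compliance and displacement may also be related to the 12-week result.

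If patients who leave are replaced and drop out of the analysis, each arm becomes a selected group, and the selection can differ between arms. An intention-to-treat rule, clearly stated and supported by follow-up, would prevent this. Section 10.1 does not supply one. Whether its sentence is meant to join the two sets by *and* or by *or*, it does not say which is primary.

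This is not a detail that can wait for a separate analysis plan. Replacement is a rule of trial conduct, and no analysis plan can recover week-12 outcomes from replaced patients who were never followed.

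**Working it through.** **1. The plan's own figure (Section 5.3).** Inputs: 96% v 77%, two-sided 5%, 80% power, 1:1, 10% drop-out. Pooled-variance formula without continuity correction:

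n per arm = [1.960·√(2·0.865·0.135) + 0.842·√(0.96·0.04 + 0.77·0.23)]² / 0.19² ≈ (0.947 + 0.391)² / 0.0361 ≈ 49.6, so 50 per arm and 100 in total.

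100 × 1.10 = 110, the stated figure. Dividing by 0.9 gives 111.1, or 112 if each arm is rounded up. The 110 is reproduced closely enough and is not in dispute.

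**2. Is replacement needed for size?** Power by normal approximation at 96% v 77%:

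| Analysed per arm | Power |
|---|---|
| 55 (all 110) | 84.0% |
| 50 | 80.3% |
| 49 | 79.5% |

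A 10% loss from 110 leaves 99, or 49 to 50 per arm. The allowance already covers missing outcomes at about 80% power, so replacement is not needed to hold the planned size.

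**3. What selective replacement could do.** This is an illustration; the inputs below are assumptions, apart from the 77% and the 110. Suppose there is no true effect, with 77% success in both arms and 55 analysed per arm. A fraction d of splint patients is removed and replaced, and a share s of those removed would have succeeded. The success rate among splint patients analysed becomes

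q = (0.77 − d·s) / (1 − d).

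Type I error is found by exact enumeration of the two-sided chi-square test, rejecting at p ≤ 0.05 as in Section 10.1. With no removal it is 5.1%.

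| d | s | q | Type I error |
|---|---|---|---|
| 5% | 0.5 | (0.77 − 0.025)/0.95 = 0.784 | 5.5% |
| 5% | 0 | 0.77/0.95 = 0.811 | 8.3% |
| 10% | 0.5 | (0.77 − 0.05)/0.90 = 0.800 | 6.8% |
| 10% | 0 | 0.77/0.90 = 0.856 | 21.2% |

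If removal is unrelated to outcome, s = 0.77, q = 0.77 and the error stays near 5%. Removing failures from the cast arm instead would raise the cast rate and work against the splint, so the sign is not determined either.

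**4. Price of analysing everyone as allocated.** Suppose a fraction of the splint arm has the cast success rate. At 5% the splint rate is 0.96·0.95 + 0.77·0.05 = 0.9505, and power at 55 per arm is 78.7%. At 10% it is 0.96·0.90 + 0.77·0.10 = 0.9410, and power is 72.9%.

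**The case against.** **Replacement need not remove anyone from the analysis.** Section 8.2 does not say that replaced patients' data are discarded. Extra enrolment alone does no harm if every randomised patient is followed and analysed as allocated. A reader might infer that intention-to-treat has become impossible or that randomisation is already lost; the documents do not support that. What stands against the plan is that it secures neither the follow-up nor the inclusion of these patients.

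**Some text limits the problem.** Section 8.1 continues follow-up after the intervention stops. Section 6.2 excludes patients who do not agree to be randomised. The flow chart in Section 7.6 places randomisation and device distribution on the same day, so there may be few randomised but untreated patients, and they are identified before any G-W score exists. This bears on the likely size but does not cure the rule. It also does not reach treated patients who withdraw later, for whom replacement is left open.

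**Section 8.3 should not be over-read.** One might infer that a patient who misses a procedure loses a week-12 score already obtained. The section says only that such patients may be classed as lost; it does not say that data are thrown away.

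**Section 10.1 may be a translation slip, and analysis sets are often defined elsewhere.** That is fair as to detail. But the sentence is present and cannot be read as fixing a primary set. A reader might infer that the set would be picked after results are seen; the documents do not show that, and the analyst is blinded.

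**Conclusion.** The point stands in this form: Section 8.2 prescribes or permits replacement after the arm is known, Section 10.1 fixes no primary population, and no section keeps replaced or withdrawn patients in the analysis of their allocated arm. The protection of randomisation for the week-12 G-W comparison is therefore not guaranteed.

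The protocol's wording on these points is certain; the size of the effect is not. No rates of non-receipt or withdrawal by arm are given, so direction and magnitude are unknown. The illustrative type I error runs from about 5% when removal is unrelated to outcome to 21.2% in the most extreme one-arm case tabulated, where 10% of splint patients are removed and all would have failed. These figures show what the rules would permit and do not predict what will happen.

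The point should be settled in the text, because it decides who enters the primary comparison of a trial in which patient and surgeon know the arm.

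**What to change.** - **Section 8.2:** delete the replacement of randomised patients and stop recruitment at 110 randomised. If extra patients are enrolled after all, state that every randomised patient stays in the analysis.
- **Section 10.1:** replace the population sentence with a statement that the primary analysis includes all randomised patients in their allocated group, and that per-protocol is supportive only.
- **Sections 8.2 and 8.3:** state that patients who do not receive or who stop the intervention are still followed for outcome to week 12, consistent with Section 8.1, and that any week-12 G-W score obtained is used.
- **Sections 8.1 and 8.2:** reconcile continued follow-up after the intervention stops with displacement as a ground for withdrawal from the study.

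The cost is a text amendment and the effort of following patients who leave treatment. No added patients are needed to cover missing outcomes, since the 110 carries that allowance. The real downside is dilution: untreated or non-compliant patients kept in the analysis pull the arms together. Under the assumption above, power at 55 per arm falls from 84% to about 79% or 73% if 5% or 10% of the splint arm has the cast success rate. The 10% allowance does not cover this, and the sponsor should accept it knowingly.
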